### Recruitment

Patients are screened for eligibility during their first consultation at our department prior to radiotherapy by a study nurse. The consulting radiation oncologist presents each eligible patient with information about the trial and answers any questions about its nature, course, benefits and risks. If radiotherapy is medically indicated and the patient provides informed consent, the patient is included in the trial. Relying on logistic considerations based on the expected annual recruitment of patients fulfilling the inclusion criteria, the recruitment period has been set at 12 months. Roughly 1000 patients are available for screening yearly, based on intrainstitutional patient statistics. This means that the likelihood of fulfilling the inclusion criteria is highly probable. On the basis of a conservative assumed consent ratio of 5%-10%, meeting the recruitment target within 12 months is realistic.

The study duration for each individual subject depends on the duration of radiotherapy, which differs with diagnosis. Typically, the period from the start of radiotherapy until the first follow-up will be between 10 and 14 weeks. A detailed timeline with interventions and assessments is illustrated in Figure 1.

### Target Population

The study population includes patients receiving radiotherapy of a primarily thoracic or pelvic target and with a curative intent. This applies to a range of malignancies and depending on diagnosis to a range of tumor stages. This approach is intended to diversify the sample on which the mobile app is tested. Examples for thoracic targets are cancers of breast and lung, whereas pelvic targets include malignancies of uterus, vagina and vulva, prostate, and rectum.

**Figure 1 figure1:**
[figure not shown]
Time-line for trial subjects. Endpoints are marked in red. EORTC QoL questionnaire: European Organisation for Research and Treatment of Cancer quality of life questionnaire.

Patients receiving a regime of chemoradiation that prospectively requires them to be treated as inpatients for a substantial portion of the duration of radiotherapy are not eligible to participate in this trial. According to standard operating procedures (SOP) at our institution, this would exclude most patients with cancers of the cervix, esophagus, anus and rectum. Exceptions from this rule are possible in individual cases (eg, patients with rectal cancer, very good clinical performance and oral chemotherapy), if the screening physician deems it feasible to conduct the treatment on an outpatient basis.

### Inclusion and Exclusion Criteria

Patients enrolled in this pilot trial must fulfill the following inclusion criteria:

Indication for radiotherapy with potentially curative intent of a primarily thoracic or pelvic targetKarnofsky performance score ≥70%Prospective ability to receive treatment as an outpatient≥18 years of age

Patients with the inability to give informed consent will be excluded from the study.

### App-Based Therapy Support

Patients will be given a mobile tablet device and will be asked to answer 5-7 differing questions. The respective answers will be collected as patient-reported outcome. This type of digital survey is conducted during clinic hours on each day prior to radiotherapy. A sample screenshot is displayed in Figure 2.

To assess the patient’s general and specific wellbeing during radiotherapy, a system of rotating questions based on the European Organisation for Research and Treatment of Cancer (EORTC) quality of life questionnaires (QLQ) has been developed. Since the wording of the questions is extracted directly from the EORTC questionnaires, which are available in multiple languages, the OPTIMISE-1 survey app will be multilingual. Depending on individual diagnosis, the patient is presented with questions extracted from the respective EORTC module (eg, BR23 for breast cancer, PR25 for prostate cancer, LC13 for lung cancer; all modules available on the EORTC website) that cover the patient’s therapy-related wellbeing, symptoms for expected toxicities and general performance. Questions are automatically rotated by the application so that by posing 5-7 questions daily, the complete module is covered within one week of therapy. A diagnosis-dependent questionnaire rotation schedule is assigned to each patient prior to the beginning of radiotherapy with the help of a Web-based backend interface. In addition to the aforementioned rotating questions, unchanging questions are posed every day at the beginning and end of the survey.

**Figure 2 figure2:**
[figure not shown]
Sample screenshot of the mobile application for patient support during radiotherapy.

For example, patients are asked to describe their general health/QoL subjectively on a 7-point scale covering a range from “excellent” to “very poor” (adapted from EORTC QLQ-C30). Furthermore, patients are asked to state whether or not they feel the need to personally consult a physician on that respective treatment day. If they do, upon completing the survey, an automatic notification is triggered at the medical-technical assistants’ management terminal, prompting them to schedule a visit with the supervising physician on that day. The information provided via the survey application is presented regularly to a supervising physician via the Web-based backend interface used for monitoring treatment and toxicity and preparing for regular patient visits. Routine check-up visits are conducted once weekly, and additional visits are arranged as requested by the patients via the app. The number and length of all visits are documented. The app-based therapy support is continued daily as long as the patient is in outpatient care.

The standard of care outside this trial at our institution for patients undergoing outpatient radiotherapy consists of weekly scheduled visits with a supervising physician and bloodwork at an interval depending on diagnosis (usually once weekly or less). The therapy support provided within this trial represents an additional, more close-knit and individualized form of care during radiotherapy.

### Assessment of Primary and Secondary Endpoints

The primary aim of this study is to assess the feasibility of an app-based therapy support. It will be assessed by the primary endpoint—the proportion of patients who answered at least 80% of the app-based questions during their radiotherapy as outpatients. For every study subject, the number of answered questions is documented on each day of radiotherapy for the assessment of the primary endpoint. This definition of feasibility was derived mainly from clinical and logistical considerations. Due to logistical difficulties unrelated to the trial (eg, personnel change, transfer of patients to different radiation units due to technical maintenance), a certain portion of treatment days is to be expected where some patients fail to receive the survey tablet device. Since there is no previous systematic data on this specific issue, we estimate the portion of those expected irregularities at a realistic 20% based on clinical experience.

The following secondary endpoints are considered:

Patient satisfactionNumber of medical consultationsDuration of medical consultations (in min)Need for toxicity-caused hospitalizationHealth-related QoL

Patient satisfaction is measured by the PSQ-18, which includes 18 items in 7 subscales: general satisfaction, technical quality, interpersonal manner, communication, early reaction to treatment side effects, time spent with doctor, accessibility and convenience. Responses to each item are given on a 5-point scale, and based on the questionnaire, a total sum score will be calculated and transformed to a scale ranging from 1 to 5.

Health-related QoL is assessed by the EORTC QLQ-C30 questionnaire in addition to the diagnosis-specific questionnaire module (eg, BR23 for breast cancer or PR25 for prostate cancer). Patients are prompted to fill out these questionnaires prior to the initiation of radiotherapy, at the time of treatment completion and at the first follow-up visit, which is routinely scheduled at 6-8 weeks after the completion of therapy. The duration and number of all visits during radiotherapy is documented to estimate the average cost of this form of therapy support. Per our SOP, the beginning and end of every consultation for all patients is documented by the physician by setting status flags within the Radiation Oncology Clinic Information System (ROKIS). The duration of every consultation can then be extracted by querying the ROKIS database. The software solutions in use for those purposes at our institution are MOSAIQ (ELEKTA, Stockholm, Sweden) for ROKIS and Crystal Reports (SAP, Walldorf, Germany) for generating database reports.

Table 1 shows the intervention and assessment schedule for the trial. The Standard Protocol Items: Recommendations for Interventional Trials (SPIRIT) checklist [12] on different protocol items related to this trial is included in Multimedia Appendix 1.

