**Objective:**

The aim of this trial (OPTIMISE-1: Oncologic Therapy Support Via Means of a Dedicated Mobile App – A Prospective Feasibility Evaluation) is to prospectively evaluate the feasibility of employing a mobile app for the systematic support of radiooncological patients throughout the course of their radiotherapy by monitoring symptoms and patient performance, and facilitating the background-exchange of relevant information between patient and physician.

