**Methods:**

The present single-center, prospective, exploratory trial, conducted at Heidelberg University Hospital, assesses the feasibility of integrating an app-based approach into patient-care during radiotherapy. Patients undergoing curative radiotherapy for thoracic or pelvic tumors will be surveyed regarding general performance, treatment-related quality of life (QoL) and symptoms, and their need to personally consult a physician by means of a mobile app during treatment. The primary endpoint of feasibility will be reached when 80% of the patients have successfully answered 80% of their respective questions scheduled for each treatment day. Furthermore, treatment-related patient satisfaction and health-related QoL is assessed by the Patient Satisfaction Questionnaire Short Form (PSQ-18) and the European Organization for Research and Treatment of Cancer (EORTC) questionnaires at the beginning (baseline) and end of radiotherapy, and at the first follow-up.

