### Statistical Analysis

The calculation of the sample size was done with respect to the primary endpoint and the primary analysis. Using the exact binomial test, we aim to show that the primary endpoint is reached at values of ≥80% of all study subjects answering ≥80% of the app-based questions during their radiotherapy as outpatients. With a sample size of 50 patients in this pilot study and an assumed percentage of 92% for the primary endpoint, a power of 1-β=80% is reached with a one-sided significance level of α=5%. Considerations regarding sample size and power were done using the *PROC POWER* procedure in SAS (version 9.4). The primary endpoint will be evaluated using the exact binomial test, which is the primary analysis. The one-sided significance level for this feasibility study is set to 5%.

Methods of descriptive data analysis will be used to describe patient characteristics and secondary outcomes, including calculation of appropriate summary measures of the empirical distribution, such as mean and standard deviation, median and interquartile range for continous variables, as well as absolute and relative numbers for categorical variables. Additionally, according to tumor type, subgroup analyses will be performed as a sensitivity analysis. Additionally, multivariable regression models will be used to analyze the relationship between patient characteristics and the primary endpoint. However, we will consider the primary variable on the original scale without any cut-off value (ie, the relative number of app-based answered questions) as the outcome variable and, thus, linear regression models will be applied. Age, gender and the need of toxicity-caused hospitalization will be included as predictors. The same model will be applied for the secondary endpoints. In addition, correlations will be considered. Graphical methods will be applied to visualize the results.

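### The outpatient-only primary endpoint can score a patient admitted early for toxicity as a full success, so alone it cannot support a whole-course feasibility claim

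*Protocol article*

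**What the plan says.** The Methods of the protocol article (Assessment of Primary and Secondary Endpoints) define the primary endpoint as "the proportion of patients who answered at least 80% of the app-based questions during their radiotherapy as outpatients". The Statistical Analysis section repeats the limit when it states the hypothesis: "the primary endpoint is reached at values of ≥80% of all study subjects answering ≥80% of the app-based questions during their radiotherapy as outpatients". The section on app-based therapy support sets the same end point for the intervention: "The app-based therapy support is continued daily as long as the patient is in outpatient care". None of these sections requires a minimum number of outpatient days or a minimum share of the planned course.

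Two other places describe a wider target. The Abstract's objective is "systematic support of radiooncological patients throughout the course of their radiotherapy", and the Study Rationale in the Discussion repeats it. The Abstract's Methods say that feasibility is reached when "80% of the patients have successfully answered 80% of their respective questions scheduled for each treatment day", with no mention of outpatient status.

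Admission is foreseen. Admission for toxicity is a secondary endpoint and a regression predictor, and Study Design says that the time of any admission will be recorded.

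**The concern.** Each patient's denominator closes on the day that outpatient care ends. Someone who answered every question for one week and was then admitted for toxicity is scored the same as someone who answered for the full course. In the first patient, app support was not carried through radiotherapy, and the reason it stopped may be related to how ill the patient became. The 20% allowance in the endpoint definition is justified by logistical irregularities unrelated to the trial, so it was not set with admissions in mind.

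At stake is what a positive result means. If feasibility is declared on the outpatient endpoint and then reported as feasibility of support over the whole of radiotherapy, the claim goes beyond the measurement. The gap lies in the patients who tolerated treatment worst.

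**Working it through.** **Step 1. Reproduce the design.** Inputs from Statistical Analysis: n=50, null proportion 0.80, assumed proportion 0.92, exact binomial test, one-sided 5%. The bar is the smallest r with P(X ≥ r | 50, 0.80) ≤ 0.05.

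- P(X ≥ 44 | 50, 0.80) = 0.1034
- P(X ≥ 45 | 50, 0.80) = 0.0480, so the bar is 45/50
- Power: P(X ≥ 45 | 50, 0.92) = 0.7919

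The stated 80% power reproduces as 79.2%. Steps 2 to 4 do not dispute it.

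**Step 2. One patient under the two denominators.** The article gives no number of treatment days, so assume 30. The patient answers everything on 5 outpatient days and is then admitted for the rest of the course.

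- Outpatient denominator: 5/5 = 100%, a success
- Planned-course denominator: 5/30 = 16.7%, a failure

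For courses of 25 to 33 days the second figure runs from 5/25 = 20.0% to 5/33 = 15.2%. The choice of course length does not change the classification. Late admissions do not matter in this way: 0.80 × 30 = 24, so a patient with 24 fully answered days before admission passes on both denominators.

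**Step 3. Sensitivity of the decision.** If 44 patients succeed on the whole-course basis and one further patient succeeds only because of the outpatient limit, the count moves from 44/50 (p=0.103) to 45/50 (p=0.048). The result changes from not shown to shown.

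**Step 4. Chance of declaring feasibility.** Suppose the true whole-course success proportion is exactly 0.80, the null value. Let m be the share of all patients who fail on the whole course but succeed under the outpatient limit. The endpoint then has success probability 0.80 + m, and the chance of declaring feasibility is P(X ≥ 45 | 50, 0.80 + m). The values of m are assumed, because the documents give no admission rate.

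| m | expected patients of 50 | success probability | chance of declaring feasibility |
|---|---|---|---|
| 0% | 0 | 0.80 | 4.8% |
| 2% | 1 | 0.82 | 9.3% |
| 4% | 2 | 0.84 | 16.8% |
| 6% | 3 | 0.86 | 28.1% |
| 8% | 4 | 0.88 | 43.5% |
| 10% | 5 | 0.90 | 61.6% |

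These are error rates for a whole-course claim. For a claim limited to outpatient time, the test keeps its exact level of 4.8%.

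**The case against.** The strongest reply is that the restriction is deliberate and coherent. Eligibility requires "Prospective ability to receive treatment as an outpatient", patients expected to be inpatients for a substantial part of treatment are not enrolled, and the app is offered only to outpatients. Questions never offered cannot fairly be called unanswered, and counting them so mixes app feasibility with toxicity. The Abstract's wording can also be read consistently, since no app questions would be scheduled during an admission. All of this stands as a defence of the outpatient endpoint as primary. It does not make that endpoint a measure of support over the whole course, and eligibility makes admission rarer without ruling it out.

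It can also be said that admission is visible elsewhere, as a secondary endpoint and as a regression predictor. That is true. However, the regression outcome is the primary variable without its cut-off, so it carries the same denominator, and neither analysis shows how many successes rest on a short outpatient stretch.

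A reader might infer more than the documents support:

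- **That a patient who merely stops using the app is scored on the early days only.** On the plain reading, a patient still receiving outpatient radiotherapy remains in the period counted, and later unanswered questions count against that patient.
- **That such patients will be dropped from the test.** Statistical Analysis refers to all study subjects, and no exclusion is proposed.
- **That the power is overstated.** The 92% was assumed for the outpatient endpoint. Applying it to a different endpoint shows the cost of redefinition and no error in the plan.

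**Conclusion.** The point holds in a limited form. The outpatient endpoint is a valid while-outpatient measure with a correctly computed power, but with no minimum exposure it can credit an early admission as a full success. By itself it cannot carry the whole-course claim in the objective. The Abstract and the Methods also word the endpoint differently, and the difference matters for these same patients.

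The size is uncertain. One patient can move the result across the 5% line. Under the assumed 2-10% range, and with true whole-course success at 80%, the chance of declaring feasibility rises from 4.8% to between 9.3% and 61.6%. These figures depend on an admission rate that the documents do not give, and only on admissions early enough to bring the patient below 80% of the planned course. It would go too far to call the primary success rate biased: for the quantity that the Methods define, it is not.

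**What to change.** 1. Keep the outpatient endpoint as primary, in all study subjects, and use the same wording in the Abstract and the Methods.
2. State that outpatient treatment days left unanswered after a patient stops using the app count as unanswered under the existing 80% criterion. Withdrawal should not be an automatic failure. On an assumed 30-day course, a patient who answered everything on 28 days (28/30 = 93%) before stopping still meets the criterion.
3. Add a sensitivity analysis that applies the same 80%/80% criterion to all treatment days of the planned course, with days after admission or early stopping counted as unanswered.
4. Report both proportions side by side, with the number of outpatient days per patient. If they lead to different conclusions, limit the feasibility claim to the time spent as an outpatient.

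The cost is some wording and a little extra analysis. Daily answer counts and the time of admission are already to be documented. The planned number of treatment days must come from treatment records, because the article does not say that it is captured. The second figure may be less favourable than the first.

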### Limitations and Future Perspectives

In the current study, the survey app is not deployed using the patient’s own mobile device but is installed on a tablet computer belonging to the investigator and integrated into the institution’s information technology infrastructure according to data protection regulations. For future trials, it is planned (after establishing feasibility and usefulness) to expand the scope of the app so that patients can use their own devices for survey completion outside the clinic.

On the other side, the aforementioned approach may contribute to addressing a possible selection bias. By presenting the application to patients on an institution-owned tablet device, we do not exclude patients who do not themselves own a mobile device, thus testing the application on patients regardless of their technical abilities and/or affinity.

The definition of feasibility in this trial is largely derived from intrainstitutional clinical experience and logistical considerations. There is, however, to date no systematic data from which a more general definition of feasibility can be derived in this context. A systematic survey conducted at our institution on oncologic patients’ use of and affinity towards mobile devices is in accordance with previously published data [13] in suggesting that roughly three quarters of patients would be inclined to use a mobile app in the context of radiotherapy. This further suggests that expecting a patient compliance of 80% to demonstrate feasibility is realistic.

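### The 92% success rate behind the sample size is not reconciled with the 20% tablet non-delivery that sets the 80% per-patient cut-off, so the stated power depends on a loss rate the protocol leaves ambiguous

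*Protocol article*

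**What the plan says.** The section Assessment of Primary and Secondary Endpoints defines the primary endpoint as "the proportion of patients who answered at least 80% of the app-based questions during their radiotherapy as outpatients". It gives clinical and logistical reasons for this definition: "a certain portion of treatment days is to be expected where some patients fail to receive the survey tablet device", for causes such as staff changes and machine maintenance, and "we estimate the portion of those expected irregularities at a realistic 20% based on clinical experience". For each day of radiotherapy, that section has the number of answered questions documented. It mentions no record of whether the tablet was handed over.

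The abstract (Methods) gives the denominator: feasibility is reached when "80% of the patients have successfully answered 80% of their respective questions scheduled for each treatment day".

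The Statistical Analysis section plans a one-sided exact binomial test of whether "the primary endpoint is reached at values of ≥80% of all study subjects answering ≥80% of the app-based questions" and sizes the trial so: "With a sample size of 50 patients in this pilot study and an assumed percentage of 92% for the primary endpoint", with 80% power at one-sided 5%. It gives no basis for 92%. Limitations and Future Perspectives calls 80% compliance realistic, citing a survey in which "roughly three quarters of patients would be inclined to use a mobile app in the context of radiotherapy".

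**The concern.** The cut-off appears to be 100% minus the expected non-delivery. If 20% is what each patient can expect to lose, a minimum requirement has been placed at an expected mean. About half of fully cooperative patients would then miss it by chance, and nothing is left for questions that patients skip. A 92% pass rate does not fit that picture.

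Two things are at stake. The 80% power holds only if 92% is realistic given the loss of tablet days, and the article does not make that connection. And if the trial misses its target, a daily count of answered questions cannot show whether the clinic failed to deliver the tablet or patients failed to respond. Those two results would lead to different next steps.

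**Working it through.** **Inputs from the protocol.** N = 50; null proportion 0.80; assumed proportion 0.92; one-sided alpha 5%; exact binomial test (Statistical Analysis). Per-patient cut-off 80% and expected irregularities 20% (Assessment of Primary and Secondary Endpoints). Denominator: questions scheduled for each treatment day (abstract).

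**Assumptions.** The number of treatment days d is not given. Recruitment puts start of radiotherapy to first follow-up at 10-14 weeks, and follow-up comes 6-8 weeks after completion. This suggests 10 - 6 = 4 to 14 - 8 = 6 weeks, or 20-30 days at five per week. The longest combination, 14 - 6 = 8 weeks, gives 40. Loss is taken as independent between days, and each day's survey as answered in full or not at all.

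**Step 1: the plan's own figure.** The smallest r with P(Bin(50, 0.80) ≥ r) ≤ 0.05 is r = 45, with exact alpha 0.048. Power is P(Bin(50, 0.92) ≥ 45) = 0.792, against a stated 80%. The figure reproduces.

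**Step 2: 20% as loss per patient-day, every offered question answered.** Pass probability = P(Bin(d, 0.80) ≥ k), where k is 0.8d rounded up.

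| Days d | Needed k | Pass probability | P(≥45 of 50 pass) |
|---|---|---|---|
| 20 | 16 | 0.630 | 0.00002 |
| 25 | 20 | 0.617 | 0.00001 |
| 28 | 23 | 0.501 | <0.00001 |
| 30 | 24 | 0.607 | <0.00001 |
| 40 | 32 | 0.593 | <0.00001 |

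Over every d from 20 to 40 the range is 0.46-0.63. If loss clusters within patients at the same 20% mean (beta-binomial; 20, 25, 30 and 40 days), the pass probability is 0.59-0.66 for intra-patient correlation 0.05-0.3, and 0.76 at 0.8. These are still well below 0.92. If patients also answer on only 95% of delivered days (daily success 0.80 × 0.95 = 0.76), passing is 0.31-0.46 at 20, 25, 28 and 30 days.

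**Step 3: the loss compatible with 92%.** Solving P(Bin(d, 1 - q) ≥ k) = 0.92 with perfect answering gives q = 0.119 (20 days), 0.124 (25), 0.110 (28), 0.128 (30) and 0.134 (40). So 92% needs a per-patient loss of about 11-13% or less.

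**Step 4: lower per-patient loss, at 20, 25, 28 and 30 days.**

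| Loss per patient-day | Answering on delivered days | Patients passing | Power |
|---|---|---|---|
| 10% | 100% | 94-97% | above the planned 79% |
| 10% | 95% | 79-87% | 3-32% |
| 5% | 95% | 95-98% | at least 96% |

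The 10% row corresponds to half the patients missing the tablet on an affected day, and the 5% row to a quarter (0.20 × 0.5 and 0.20 × 0.25). Neither share is in the protocol. If the 95% applies to single questions, at an assumed 6 per day, the 10% loss row gives 82-85% passing and 9-24% power.

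**Step 5: power by true pass rate.** P(Bin(50, p) ≥ 45) is 0.219 at p = 0.85, 0.435 at 0.88, 0.616 at 0.90 and 0.792 at 0.92.

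**The case against.** The strongest reply is that the protocol never gives a per-patient delivery rate. It speaks of days on which some patients go without the tablet. Read literally, about 20% of days are affected, and on those days only part of the patients miss out. Per-patient loss is then below 20%, and step 4 shows that 92% can be reached. The 20% could also be an upper allowance that the cut-off is meant to absorb. This stands. A reader might infer from step 2 that 92% is impossible, or that the trial is bound to fail on its own figures. The documents do not support that, because it needs the per-patient reading of the 20%, which the text does not fix. Nor is there an arithmetic error: the power calculation is right for the inputs it states.

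A second reply is that delivery belongs to feasibility. The aim is to integrate the app into patient care, so a clinic that does not hand out the tablet has shown something relevant, and counting all scheduled days is a defensible primary choice. This also stands. It argues against replacing the primary endpoint, but not against recording delivery separately.

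A third concerns the survey. Since three quarters is below the 80% null, a reader might take 75% as the trial's expected pass rate. That does not follow. The survey concerns inclination among patients in general, while the trial enrols only those who consent (5%-10% assumed under Recruitment). The survey sentence is weak support for 80%, but it does not predict failure.

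None of these replies supplies a basis for 92% or connects it to the 20%.

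**Conclusion.** The concern holds as an unreconciled planning assumption. The cut-off is explained by 20% irregularities, the abstract counts every scheduled question, and 92% is assumed without reference to either. If 20% is the loss per patient-day, 92% is implausible even with perfect answering: 46-63% of patients pass under independent loss over 20-40 days, and success in the trial is close to impossible. At about 11-13% loss, 92% is just reached with perfect answering. At 5% loss with 95% answering, the trial has at least 96% power at the course lengths examined. Power therefore runs from near zero to above 95%, depending on one quantity the protocol leaves open. These figures rest on the assumed number of treatment days, independent loss and all-or-nothing daily response. Separately, with only answered questions documented, a missed target could not be attributed to delivery or to patients.

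**What to change.** 1. Record for each treatment day whether the tablet was handed over, with the reason if not.
2. Keep the all-scheduled-days endpoint as primary if overall feasibility is the question. Pre-specify beside it the same 80% criterion on delivered days, and the delivered share of treatment days with a confidence interval.
3. In Assessment of Primary and Secondary Endpoints, state what the 20% refers to (days with any irregularity, or loss per patient-day), and name the denominator there and in Statistical Analysis as the abstract does.
4. In Statistical Analysis, either justify 92% against that loss or give power over plausible true rates: 22% at 85%, 44% at 88%, 62% at 90%, 79% at 92%.

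The cost is one yes/no field per treatment day (plus a reason when the tablet was not handed over), some wording, and a less favourable power statement. The sample size and the primary test need not change.
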